### Plans to promote participant retention and complete follow‐up

To increase participant retention rates, several strategies will be employed. Participants will be informed that in addition to the use of SPSRS, baseline, 3‐week, and 5‐week post‐intervention outcome measurements will be provided free of charge. Besides that, participants can freely select videos to watch. Because waiting‐list control group participants might wish to receive the video‐viewing intervention, they will be informed that they can receive it when the formal trial ends after 5 weeks. All participants who complete the outcome measurements at 3 and 5 weeks after the intervention begins will receive a total of 200 redeemable points (100 at each measurement point) from the market research company that may be used to obtain gift cards or cryptocurrency.^69^ These incentives compensate participants for the time spent responding to each survey and are provided to maximize data collection for verifying intervention effects. Furthermore, these incentives will serve to mitigate risks such as gaming fund diversion and reward misuse.^69^ In addition, since other expenses such as data charges and electricity bills are expected to be higher in the intervention group than the waiting‐list control group, participants in the intervention group will receive an additional 2300 points if they respond to scheduled outcome measurements 3 and 5 weeks after the intervention begins based on a contract with the market research company.

All outcome assessments will be conducted via online surveys to accommodate participants' schedules. To encourage continued participation at each survey point (3 and 5 weeks after the intervention begins), reminders will be sent via email through the market research company to participants who have not completed the survey. Reminders will be sent once per day for a maximum of 2 days following the initial request.

Online surveys are configured to prevent incomplete responses, thereby addressing data loss. Participants who meet criteria for intervention refusal or discontinuation will be asked to provide data and participate in outcome assessments at 3 and 5 weeks after intervention initiation. These explanations and requests will be emphasized and explained during the electronic informed consent process.

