### Blinding

Due to the intervention's nature, blinding of participants and therapists is not possible, so only evaluators will be blinded. Baseline assessments will be performed before randomization. Additionally, to maintain evaluators' blinding, assessments at 3 and 5 weeks after the intervention begins will be automatically sent to participants via a templated online questionnaire provided by the market research company. Because the trial blinds only evaluators, the need for emergency unblinding is expected to be extremely low.

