#### Center for Epidemiologic Studies Depression Scale

The CES‐D (Japanese version) is a 20‐item self‐report questionnaire that measures depressive symptoms on four subscales: (1) somatic and retarded activity; (2) depressed affect; (3) positive affect; and (4) interpersonal problems.^31^ The CES‐D uses a four‐point Likert scale (A ≤ 1 day, B = 1–2 days, C = 3–4 days, and D = 5–7 days), with each item scored from 0 to 3. Total scores range from 0 to 60, with higher scores indicating more severe depressive symptoms. The CES‐D's reliability and validity have been verified.^31^, ^61^, ^62^, ^63^, ^64^

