### Sample size

In the previous 5‐week pilot RCT, Hedge's g for CES‐D scores between the SPSRS and control groups was 0.61.^25^ However, pilot studies have been shown to overestimate results.^34^, ^35^, ^36^ Therefore, considering a Hedge's *g* of 0.4, a two‐sided significance level of 5%, and a power of 80%, the sample size was calculated at 100 participants per group, totaling 200. Furthermore, internet‐based studies have reported dropout rates of 30%, and a systematic review of RCTs in smartphone apps for depression indicated a dropout rate of 47.8% after adjustment for publication bias.^70^, ^71^ Therefore, assuming a 50% dropout rate, this trial's sample size, using the pwr package in R (version 4.5.1), was calculated at 200 participants per group, totaling 400.

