#### Analysis of primary and secondary outcomes

Data analysis will be based on ITT analysis. Therefore, participants will be analyzed based on their initial group assignment regardless of adherence to the intervention. Assuming primary outcome data are randomly missing, the trial will use a linear mixed model (LMM) with restricted maximum‐likelihood estimation to compare mean changes between the experimental and waiting‐list control groups from baseline to Week 5.^72^ LMM can address defects arising in clinical trials and use all available data to estimate results, thereby making it possible to compare the experimental group that addressed the missing data to the waiting‐list control group.^72^

The CES‐D score is the dependent variable; the independent variables are group (experimental or control), time (baseline, 3 weeks, 5 weeks), and interaction between group and time—all treated as fixed‐effect factors, with participants treated as random‐effect factors. Baseline CES‐D scores will be included as covariates in the LMM. Additionally, to confirm results' robustness for the primary outcome, sensitivity analyses will be conducted using multiple imputation methods and per‐protocol analyses only for participants who provided complete data.^73^ Statistical significance will be set at *p* < 0.05 using a two‐tailed test. Additionally, Hedge's *g* will be calculated as the effect size between the two groups.^74^, ^75^ Secondary outcomes will be analyzed using the same procedures as primary outcomes; however, due to secondary outcomes' exploratory nature, no adjustments for multiple comparisons will be performed. No subgroup analyses are currently planned. LMM calculations will use the lmerTest package, and Hedge's *g*‐statistic will be calculated using the compute.es package. Multiple comparisons will be performed using the mice package.

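### Answering the outcome surveys earns 2,500 points in the experimental arm and 200 in the control arm: an avoidable arm-specific incentive to respond

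*Protocol article*

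**What the plan says.** In the protocol article, under Plans to promote participant retention and complete follow-up, participants who complete the week 3 and week 5 measurements "will receive a total of 200 redeemable points (100 at each measurement point"). This applies to both arms, and its purpose is stated: "These incentives compensate participants for the time spent responding to each survey", and to maximise data collection.

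The same paragraph then says that "participants in the intervention group will receive an additional 2300 points if they respond to scheduled outcome measurements" at weeks 3 and 5. The reason given is cost: "since other expenses such as data charges and electricity bills are expected to be higher in the intervention group" than in the control arm. Neither viewing time nor expense incurred is a condition of the payment.

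Three other statements bear on this:
- Under Blinding: "blinding of participants and therapists is not possible, so only evaluators will be blinded". The primary outcome, the CES-D, is a self-report questionnaire.
- Under Sample size, a single 50% dropout rate is assumed, with no arm-specific value.
- Under Analysis of primary and secondary outcomes, the linear mixed model is introduced with "Assuming primary outcome data are randomly missing". The sensitivity analyses named are multiple imputation and a per-protocol analysis of participants with complete data.

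The limitations in the Discussion cover lack of blinding and waiting-list disappointment, but not the unequal payment.

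**The concern.** The payment is described as cost compensation but works as a response incentive. An experimental participant who never opens the website but answers both surveys meets the condition. One who views for five weeks and skips the surveys does not. Since the protocol uses points to maximise data collection, it expects points to affect who answers.

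About half of the week 5 outcomes are expected to be missing. A large payment may bring in reluctant responders in one arm while a small one leaves mainly the willing in the other. If willingness is related to current mood, the two sets of responders are no longer comparable in a way the observed data can correct. The mixed model assumes this does not happen. Multiple imputation in its standard form makes the same assumption, and the complete-data analysis is exposed to the same selection, so neither tests the risk.

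**Working it through.** **The plan's own figures.** At a standardised difference of 0.4, two-sided 5% and 80% power, the t-based sample size is 99.08, rounded up to 100 per group. Allowing for 50% dropout, 100/(1 − 0.5) = 200 per group. The protocol's numbers reproduce and are not in dispute.

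**Payment ratio.** (200 + 2,300)/200 = 12.5, reading the 2,300 points as one payment on top of the 200.

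**Does unequal response by itself cause bias?** No. Group is a fixed effect in the model, so response that differs by arm, or by arm and observed scores, is still missing at random. Null simulations (200 per arm, assumed correlation 0.5 between visits) with 65%/35% response gave:
- response dependent on arm only: bias 0.00 SD, type I error 4.4% to 4.8%;
- response dependent on baseline and week 3 scores: bias 0.00 SD, error 4.6%, or 5.4% if only controls respond in that way.

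**What if response also depends on the unseen week 5 score?** The response rates and the strength of dependence below are assumptions; the protocol gives neither. The dependence is log-odds 0.5 per SD unless stated otherwise. Response is given as experimental/control.

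| Response | Dependence | Data used | Bias (SD) | Type I error |
|---|---|---|---|---|
| equal | same in both arms | baseline | 0.00 | 4.7% |
| 60%/50% | same in both arms | baseline, week 3 | 0.03 | 5.9% |
| 65%/35% | same in both arms | baseline, week 3 | about 0.10 | 12% |
| 65%/35% | same in both arms | baseline | 0.11 | 15% |
| 65%/35% | controls only, 0.3 to 0.5 | baseline | 0.14 to 0.23 | 19% to 44% |
| 65%/35% | controls only | baseline, week 3 | 0.21 | 40% |
| 50%/50% | controls only | baseline, week 3 | 0.16 | 26% |

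A separate repeated-measures simulation at 65%/35%, with the same dependence in both arms, gave 0.08 SD and 8%, which lies inside the range. The last row shows that most of the bias in the controls-only scenarios comes from the assumed mechanism, since it persists when response rates are equal.

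**Closed-form cross-check.** For a plain comparison of completers under a normal selection model, the responder mean in an arm with response p is shifted by ρφ(c)/p, where c = z(1 − p) and ρ is the correlation between response and outcome. At ρ = 0.2 and 60%/50%: φ(0)/0.5 = 0.798 and φ(−0.253)/0.6 = 0.644, so the bias is 0.2 × (0.798 − 0.644) = 0.03 SD. The standard error is √(1/120 + 1/100) = 0.135 and the type I error 5.6%. At 70%/50% the figures are 0.06 SD and 7.5%; at 80%/50%, 0.09 SD and 10.8%.

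**Direction.** If better-off people respond more in both arms, the less responsive control arm looks too well and the bias runs against the intervention. If worse-off people respond more, it favours the intervention.

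**Relative to the design.** The plan is built by "considering a Hedge's *g* of 0.4". A bias of 0.03 to 0.11 SD is 0.03/0.4 = 8% to 0.11/0.4 = 28% of that effect.

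**The case against.** The strongest defence is that the extra pay may balance the arms. Experimental participants are asked for at least 350 minutes of viewing and controls for nothing, so without extra pay the experimental arm might lose more people. Controls also have an incentive of their own, since they are offered the website after the week 5 questionnaire. This stands as a possibility, and it is why differential attrition cannot be called established. But the protocol does not give balance as the purpose of the payment, and nothing shows that 2,300 points was set to achieve it.

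A reader might infer four stronger things, which the documents do not support:
- **That unequal response breaks the missing-at-random assumption.** It does not, because group is in the model. Dependence on the unseen score is also needed.
- **That type I error is inflated to 30% or more.** Figures of that size need dependence in controls only, together with a 65%/35% split that has no source in the protocol.
- **That power is lost.** Power falls from 80.4% to 76.6% at 130/70 responders only because the total is held at 200. If controls stay at 50% and the paid arm rises to 70% (140/100), power is 86.1%.
- **That participants are paid to report improvement.** Payment depends on responding, not on the score. The lack of participant blinding is a separate problem, which the protocol acknowledges.

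The protocol also does not fix the assumptions of the multiple imputation, and a separate analysis plan may do so. The criticism of the sensitivity analyses therefore applies to standard multiple imputation and to the complete-data analysis as named.

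**Conclusion.** The point holds as a designed-in difference in the incentive to respond, not as demonstrated attrition or bias. The 12.5 ratio, the condition on answering, the open-label self-report and the 50% planned dropout are all in the text. The harm is conditional: it needs response that differs by arm and also depends on the unobserved week 5 score, which is plausible for a depression scale but not established. Under the assumptions shown, with the same moderate dependence in both arms, bias is roughly 0.03 to 0.11 SD and type I error about 6% to 15%. It is larger if the dependence differs by arm. The direction is unknown, so the bias could not be reliably corrected afterwards. A cheap change removes the cause, so this should be fixed, but it does not invalidate the trial.

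**What to change.** 1. Make the payment for completing the outcome surveys identical in both arms.
2. Pay any data-cost compensation on a basis not tied to questionnaire response, for example a fixed amount to every experimental participant. This must follow randomisation: under Study setting and recruitment timeline, participants are enrolled before they are allocated, so an arm-specific payment at enrolment is not possible. Alternatively, split the same response-contingent budget equally between the arms.
3. Report response by arm at weeks 3 and 5.
4. Add a delta-adjusted (missing-not-at-random) sensitivity analysis for the primary outcome, in particular for participants already enrolled under the unequal payment.

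**Cost.** A contract change with the survey company and an ethics amendment are needed, and response in the experimental arm may fall. In points:
- At 50% response the present rule costs 100 × 2,300 = 230,000. The same sum spread over all 200 experimental participants is 230,000/200 = 1,150 each, which is budget-neutral.
- Paying the full 2,300 unconditionally costs 200 × 2,300 = 460,000. That is 230,000 more than now at 50% response, or 460,000 − 130 × 2,300 = 161,000 more at 65%.
- Raising controls to the same response-contingent amount costs at most 200 × 2,300 = 460,000 more, if every control responds.

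Recruitment is planned until March 2030, so an amendment could still cover participants not yet enrolled.

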### Sample size

In the previous 5‐week pilot RCT, Hedge's g for CES‐D scores between the SPSRS and control groups was 0.61.^25^ However, pilot studies have been shown to overestimate results.^34^, ^35^, ^36^ Therefore, considering a Hedge's *g* of 0.4, a two‐sided significance level of 5%, and a power of 80%, the sample size was calculated at 100 participants per group, totaling 200. Furthermore, internet‐based studies have reported dropout rates of 30%, and a systematic review of RCTs in smartphone apps for depression indicated a dropout rate of 47.8% after adjustment for publication bias.^70^, ^71^ Therefore, assuming a 50% dropout rate, this trial's sample size, using the pwr package in R (version 4.5.1), was calculated at 200 participants per group, totaling 400.

### Statistical analysis

The latest version of R will be used for data analysis.

#### Analysis of primary and secondary outcomes

Data analysis will be based on ITT analysis. Therefore, participants will be analyzed based on their initial group assignment regardless of adherence to the intervention. Assuming primary outcome data are randomly missing, the trial will use a linear mixed model (LMM) with restricted maximum‐likelihood estimation to compare mean changes between the experimental and waiting‐list control groups from baseline to Week 5.^72^ LMM can address defects arising in clinical trials and use all available data to estimate results, thereby making it possible to compare the experimental group that addressed the missing data to the waiting‐list control group.^72^

The CES‐D score is the dependent variable; the independent variables are group (experimental or control), time (baseline, 3 weeks, 5 weeks), and interaction between group and time—all treated as fixed‐effect factors, with participants treated as random‐effect factors. Baseline CES‐D scores will be included as covariates in the LMM. Additionally, to confirm results' robustness for the primary outcome, sensitivity analyses will be conducted using multiple imputation methods and per‐protocol analyses only for participants who provided complete data.^73^ Statistical significance will be set at *p* < 0.05 using a two‐tailed test. Additionally, Hedge's *g* will be calculated as the effect size between the two groups.^74^, ^75^ Secondary outcomes will be analyzed using the same procedures as primary outcomes; however, due to secondary outcomes' exploratory nature, no adjustments for multiple comparisons will be performed. No subgroup analyses are currently planned. LMM calculations will use the lmerTest package, and Hedge's *g*‐statistic will be calculated using the compute.es package. Multiple comparisons will be performed using the mice package.

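### The primary mixed model uses baseline CES-D both as an outcome row and as a covariate, so under the planned 50% dropout its nominal 5% test runs at roughly 8–15%, depending on visit correlations and dropout timing that the protocol does not give

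*Protocol article*

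**What the plan says.** The section on analysis of primary and secondary outcomes makes the CES-D score, not its change, the dependent variable, and states that "the independent variables are group (experimental or control), time (baseline, 3 weeks, 5 weeks), and interaction between group and time" enter as fixed effects. Participant is the only random effect. The same paragraph says that baseline CES-D "scores will be included as covariates in the LMM". Fitting is by restricted maximum likelihood in lmerTest, all available data are used, and the aim is to compare mean change from baseline to week 5. Secondary outcomes follow the same procedure.

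The sample size section sets a "significance level of 5%, and a power of 80" per cent, finds 100 per group, and doubles this by "assuming a 50% dropout rate". Read literally, the primary model is CES-D ~ group × time (baseline, week 3, week 5) + baseline CES-D + random intercept for participant.

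**The concern.** A baseline value can be one of the repeated outcomes or a covariate. When it is both, every baseline row is partly predicted by itself. Those rows have far less residual variance than the follow-up rows, but the model assumes one common residual variance.

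With complete data this does little harm to the week-5 interaction. With heavy dropout it matters, because every dropout still contributes a baseline row while follow-up rows become scarce. The pooled variance is then weighted towards rows that carry almost no noise, and the noisy week-5 mean gets too small a standard error. This is the trial's only confirmatory test, so its p-value would overstate the evidence and its confidence interval would be too narrow.

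**Working it through.** **The plan's own figure.** With d = 0.4, two-sided 5% and 80% power, n = 2(1.960 + 0.842)²/0.4² = 98.1, so 99 per group by the normal formula. The t-based solution is 99.08, rounded up to 100, which gives 80.7% power. Then 100/(1 − 0.5) = 200 per group. The stated figures ("the sample size was calculated at 100 participants per group, totaling 200", and after dropout "was calculated at 200 participants per group, totaling 400") reproduce. The problem lies in the model, not in the sample size.

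**Inputs.** From the protocol: 200 per arm, 50% dropout by week 5, the model above, two-sided 5%. Assumed, because the protocol is silent: visit correlations, the share already lost by week 3, and normal scores with SD 1 (baseline SD varied from 0.7 to 1.0).

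**Mechanism by hand.** Take equal correlations of 0.5, with 30% lost by week 3 and 50% by week 5. The simulated fits averaged a baseline slope γ = 0.733, random-intercept variance 0.032 and residual variance 0.437, a total of 0.469.

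- True residual variance on a baseline row: (1 − γ)² = 0.267² = 0.071.
- True residual variance on a follow-up row: 1 + γ² − 2γ(0.5) = 1 + 0.537 − 0.733 = 0.804.
- Rows available: 400 baseline, 280 at week 3, 200 at week 5. Pooled: (400 × 0.071 + 480 × 0.804)/880 = 0.471, in line with the fitted 0.469.

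So a week-5 row is given variance 0.47 when it has 0.80. The random-intercept variance is small, so treat rows as independent as an approximation:

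- Model SE of the week-5 contrast: √[2 × 0.469 × (1/100 + 1/200)] = 0.119.
- True SE: the covariance term is 0.267 × (0.5 − 0.733) = −0.062, so √{2 × [0.804/100 + 0.071/200 + 2 × 0.062/200]} = 0.134.

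The simulation gave 0.116 against 0.131. An SE ratio of 0.885 implies a true level of P(|Z| > 1.96 × 0.885) = 8.3%; the simulated level was 8.6%.

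**Simulated level of the group × week-5 test under no effect.** Correlations are listed as baseline–week 3 / baseline–week 5 / week 3–week 5. Dropout is completely at random.

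| Correlations | Missing at week 3 / week 5 | Model SE / true SE | Level |
|---|---|---|---|
| 0.3 / 0.3 / 0.3 | 30% / 50% | 0.136 / 0.152 | 8.3% |
| 0.5 / 0.5 / 0.5 | 30% / 50% | 0.116 / 0.131 | 8.6% |
| 0.5 / 0.5 / 0.5 | 35% / 50% | 0.115 / 0.134 | about 9–10% |
| 0.6 / 0.5 / 0.7 | 30% / 50% | 0.105 / 0.131 | 11.6% |
| 0.6 / 0.5 / 0.7 | 35% / 50% | 0.104 / 0.133 | about 12% |
| 0.6 / 0.5 / 0.7 | all 50% lost by week 3 | 0.101 / 0.133 | 13.8% |
| 0.7 / 0.6 / 0.75 | all 50% lost by week 3 | 0.090 / 0.122 | 14.8% |
| 0.5 equal, or 0.6 / 0.5 / 0.7 | 20% / 30% | – | about 7–10% |
| equal | none | – | about 5% |
| falling with time | none | – | about 8% |

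Runs used 1000 to 3000 trials. Monte Carlo error at a level of 10% is √(0.1 × 0.9/3000) = 0.5 points, or 0.9 points with 1000 trials. The REML code agreed with a standard mixed-model routine on a test data set (coefficient −0.0859, SE 0.1502 in both). Dropout that depended on baseline, or differed between arms (40%/60%), gave 10.9–13.0%.

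**Which part causes what.** At 50% dropout:

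- Drop the covariate, keep the baseline row and random intercept: about 4.5–5.6% with equal correlations, 6.5–8.7% when correlation falls with time.
- Drop the baseline row, keep the covariate and random intercept: about 4–7% throughout.
- Drop the baseline row, keep the covariate, use an unstructured covariance: 4.6–5.6%.

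The double use of baseline therefore causes most of the excess. The random-intercept covariance adds a smaller, separate part when correlation falls with time.

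**The case against.** Six points can be made for the plan.

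- **The size rests on inputs that the protocol does not give.** This stands. Only the overall 50% is stated, as a cautious value next to a cited 30%, and reminders and incentives may keep dropout lower. A reader might infer one firm inflated level; the documents support only a conditional range. At 5%/10% missing, the level was 5.4% with equal correlations and 7.8% with falling ones.
- **The model is not invalid in itself.** This stands. The estimate stays centred, and with complete data and equal correlations the test holds its level. It is tempting to blame the fall of the random-intercept variance towards zero, but that also happens with complete data (0.055 instead of 0.50), where the level is 5.1%. The inflation needs the baseline-only rows.
- **Part of the excess is an ordinary simplification.** This stands. With complete data and falling correlation the level is about 8% with or without the covariate. That part belongs to the random intercept.
- **Power is not lost against the plan.** This stands. A reader might infer that the trial is underpowered. With 100 complete cases per arm the written contrast had 80.6% power, which meets the stated 80%. Proper baseline adjustment gave 90.7% at an assumed correlation of 0.5, which is a bonus.
- **The sensitivity analyses might expose the fault.** This stands in part. The same model on complete cases had a level of 4.8% with equal correlations (7.9% with falling ones), so a discrepancy could show. It would not repair the primary p-value.
- **A fuller analysis plan may state the model differently.** This does not remove the point. The article names the outcome, time levels, covariate, random effect and package, and nothing in it restricts the outcome rows to follow-up.

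**Conclusion.** The primary model is wrong as written and should be changed before analysis. At the planned 50% dropout the two-sided 5% test runs at roughly 8–15%. With 35%/50% missing it is about 9–10% for equal correlations of 0.5 (SE about 14% too small) and about 12% for 0.6/0.5/0.7 (SE about 20–22% too small). It is higher if all losses come before week 3. These figures assume normal scores and the stated correlations and week-3 losses. Every scenario run at 50% dropout gave more than 8%. The excess shrinks as dropout falls, and is absent with complete data and equal correlations.

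**What to change.** Use baseline once. Take weeks 3 and 5 as the only outcome rows, with group, week, group × week and baseline CES-D as fixed effects, and name the week-5 group difference as the primary contrast. This can stay in lmerTest with a random intercept.

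A cheap refinement, which removes the remaining excess, is an unstructured within-person covariance (mmrm or nlme::gls) with a baseline × week term. Alternatively, keep baseline as an outcome row, drop the covariate and constrain the baseline means to be equal; in that case the unstructured covariance is needed, not optional. Apply the same model to K6 and GAD-7.

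The cost is a change of analysis wording, a different R package if the refinement is taken, and a p-value less favourable than the miscalibrated one. No new data and no change of sample size are needed.

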### Study setting and recruitment timeline

This trial will recruit participants from the panel network (36 million members) of a Japanese market research company (Macromill Group, Tokyo) from October 1, 2025, to March 31, 2030. The research firm will email invitations to panelists aged 18–64, explaining the trial's purpose and procedures. The invitation will include an electronic consent option; individuals who check “consent” will be deemed to have agreed to participate in the main trial and can proceed to the online questionnaire for eligibility assessment. Participants who meet eligibility criteria will then undergo a baseline assessment and be considered enrolled. By the Central Registration Center at Kagoshima University, they will subsequently be randomly assigned to the experimental or the waiting‐list control group. Participants will be scheduled to complete Japanese versions of the CES‐D, Kessler Screening Scale for Psychological Distress (K‐6), and Generalized Anxiety Disorder‐7 (GAD‐7) questionnaires at 3 and 5 weeks after the intervention begins.^31^, ^46^, ^47^, ^48^, ^49^ Additionally, at 5 weeks after the intervention begins, the Global Rating of Change (GRC) scales will be assessed in addition to the CES‐D, K6, and GAD‐7.^50^, ^51^ The CES‐D will be administered during the main trial's eligibility assessment, while the K6 and GAD‐7 will be administered during baseline assessment. At 3 weeks after the intervention begins, assessments will be conducted in the following order: CES‐D, K6, and GAD‐7. At 5 weeks, assessments will be conducted in the following order: CES‐D, K6, GAD‐7, and GRC scales. Demographic information and lifestyle characteristics will be assessed only at baseline. Figure 1 shows the study's flowchart, and Table 1 shows the assessment schedule.

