### Allocation

Following baseline assessment, participants will be randomly assigned to the experimental group or the waiting‐list control group in a 1:1 ratio. The randomization list will be generated by an independent third party using the blockrand package in R (version 4.5.1) with a replacement block method of appropriate size. To ensure allocation concealment, the block size will not be disclosed until the trial ends. The generated randomization list will be managed at the Central Registration Center at Kagoshima University, and participants will be randomly assigned after completing the baseline questionnaire. These procedures will prevent selection bias.

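### With 50% dropout allowed for, the primary mixed model conditions only on CES-D; adding the baseline K6, GAD-7, age and gender already collected would weaken the missing-at-random assumption at no data cost (optional improvement)

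*Protocol article*

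**What the plan says.** Under Analysis of primary and secondary outcomes, the article specifies the primary model in full. CES-D is the dependent variable. Group, time (baseline, week 3, week 5) and their interaction are fixed effects, and participant is a random effect. Baseline CES-D "scores will be included as covariates in the LMM". No other covariate is named. The handling of missing data rests on one premise: "Assuming primary outcome data are randomly missing". Secondary outcomes follow the same procedures.

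The Sample size section expects many missing outcomes: "assuming a 50% dropout rate", the target is doubled from 100 to 200 per group.

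More is known about each participant than CES-D. Study setting and recruitment timeline places K6 and GAD-7 in the baseline assessment and adds: "Demographic information and lifestyle characteristics will be assessed only at baseline". Data collection lists gender, age, sleep, exercise, drinking and smoking, and says that the forms reject incomplete answers. Under Allocation, randomisation follows the baseline questionnaire. These variables should therefore be complete and unaffected by treatment.

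**The concern.** A likelihood-based mixed model is valid under missing at random given what the model contains. Here that is group, time and the observed CES-D values. If people with more distress or anxiety, or of a certain age or gender, leave at different rates in the two arms, and if those traits also predict week-5 CES-D beyond the CES-D already observed, then those still observed in the two arms are no longer comparable given the model, and the week-5 difference is biased.

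The design gives some reason to think about this. Only the experimental arm has a daily viewing task, and only that arm receives 2300 extra points for answering the surveys. The Discussion also treats anxiety and distress as relevant to progression alongside depressive symptoms. With up to half of the primary outcomes allowed to be missing, the result leans on the assumption, and the data that would weaken it are already in hand.

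**Working it through.** **1. The plan's own figures.** Inputs from Sample size: standardised effect 0.4, two-sided 5%, power 80%. Normal approximation: n = 2 × (1.960 + 0.842)² / 0.4² = 98.1, so 99 per group. The two-sample t-test gives 99.08, so 100, as stated ("the sample size was calculated at 100 participants per group, totaling 200"). Allowing for dropout: 100 / (1 − 0.5) = 200 per group, as stated ("was calculated at 200 participants per group, totaling 400"). Power at 100 completers per group is 80.4%. Both figures reproduce, and neither uses a covariate gain.

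**2. When omission produces bias.** Let X be an omitted baseline covariate (SD 1) with partial effect b on week-5 CES-D given baseline CES-D, and let dropout have log-odds slope a_E and a_C on X in the two arms. Among completers, at 50% dropout, the mean of X shifts by at most a/2 in each arm, because p(1−p) ≤ 0.25 and 0.25/0.5 = 1/2. Adjusting for baseline CES-D, correlated r with X, leaves roughly a share 1 − r². So

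bias ≈ b × (1 − r²) × (a_E − a_C) / 2.

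This is zero if the slopes are equal or if b = 0. Both conditions are needed.

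**3. Size under assumed associations.** The documents give no value for b, r or the slopes. Assumed: b = 0.2 to 0.3, r = 0.4, true effect 0.40 SD, 50% dropout. By hand, for an odds ratio of 1.5 in one arm: (ln 1.5)/2 = 0.203; × 0.84 = 0.170; × 0.2 to 0.3 = 0.03 to 0.05.

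The formula describes completers only. The planned model also uses week-3 CES-D from those who leave later, so it was simulated directly: a random-intercept model on weeks 0, 3 and 5 with baseline CES-D as covariate. Two sets of timing assumptions were used: 60% of dropout before week 3; and half before week 3 with residual correlation 0.6 between weeks 3 and 5. Simulation error is about 0.01.

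| Dropout odds ratio per SD of X | Completers only, by hand | Completers only, simulated | Planned model | Planned model plus X and X × time |
|---|---|---|---|---|
| Equal in both arms | 0.40 | no bias | 0.40 | 0.39–0.42 |
| 1.5 in one arm, none in the other | 0.43–0.45 | 0.44–0.45 | 0.40–0.43 | 0.39–0.42 |
| 1.5 and 0.67 | 0.47–0.50 | 0.46–0.50 | 0.42–0.46 | 0.39–0.42 |
| 2.0 and 0.5 | 0.52–0.57 | 0.51–0.57 | 0.44–0.49 | 0.39–0.42 |

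At b = 0.1 the planned model gave 0.40 in every pattern. The slopes here inflate the effect; reversing them would shrink it.

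**4. Harsher inputs.** A third simulation took X correlated 0.6 with baseline CES-D, residual effects of 0.15 to 0.40 SD, and log-odds slopes of 0.5 to 1 acting at both stages of dropout. The bias in the planned model was 0.03 to 0.17 SD with dropout linked to X in one arm only, 0.08 to 0.20 SD with opposite slopes (+0.5 and −0.5), and within simulation error of zero with equal slopes.

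**5. Form of the adjustment.** Baseline CES-D is both an outcome time point and a covariate, so a single main effect of X fits weeks 0, 3 and 5 badly. A main effect alone left up to 0.03 SD of bias under the inputs of step 3 and about 35% to 60% of it under step 4. The time interaction is needed.

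**6. Precision.** If the added covariates explain a further share ΔR² of the outcome variance, SE is multiplied by √(1 − ΔR²).

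| ΔR² (assumed) | SE ratio | Power at 100 completers per group |
|---|---|---|
| 0 | 1 | 80.4% |
| 0.05 | 0.975 | 82.3% |
| 0.10 | 0.949 | 84.3% |

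**The case against.** The case for leaving the model alone is substantial. Adjusting for the baseline value of the outcome under a stated missing-at-random assumption is a legitimate prespecified analysis, and nothing in the article is misstated or contradictory on this point. K6 and GAD-7 overlap with CES-D and may add little. The 50% is a planning allowance above the cited 30% and 47.8%, not a forecast of missing outcomes. People who stop the intervention are still asked for their outcomes, with reminders and points. All of this stands, and it is why the point is optional.

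Three stronger readings are tempting and are not supported.

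- A reader might infer that leaving these covariates out biases the week-5 difference. It does not unless both conditions in step 2 hold. The unequal task and the extra points could make dropout rates differ by arm. They do not show that distress, anxiety, age or gender relate to dropout differently by arm. The opposite-slope patterns in particular have no support in the documents.
- A reader might size the problem from a completers-only regression and reach 0.44 to 0.57. That is not the planned analysis. The planned model gives 0.40 to 0.49 for the same inputs. Part of that reduction comes from the double use of baseline CES-D, a separate matter, and should not be read as protection.
- A reader might infer that the trial loses power. The sample size assumes an unadjusted comparison, so this is a gain not taken, not a shortfall.

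Multiple imputation is planned as a sensitivity analysis. Which variables it uses is ordinary analysis-plan detail, and its absence from the article is no finding.

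**Conclusion.** The point holds in a conditional form. The primary model is fully stated, it conditions only on group, time and CES-D, and it thereby assumes more about the missing outcomes than the collected data require. The possible bias runs from nil (equal dependence in both arms, or a weak covariate) through up to about 0.03 SD (odds ratio 1.5 in one arm) to 0.04 to 0.09 SD (odds ratios 2.0 and 0.5), against a planned effect of 0.4. The harsher inputs reach 0.20 SD. Each of these rests on assumed associations, and the direction is unknown. The precision gain is modest: for ΔR² of 0.05 to 0.10, SE is 2.5% to 5% smaller and power about 82% to 84% instead of 80.4%. The stated sample size and power are sound as they are. This is an optional improvement, not an error.

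**What to change.** Add one sentence to the analysis section: baseline K6, baseline GAD-7, age and gender enter the primary model as fixed covariates alongside baseline CES-D, each with its interaction with time. Use the same set in the secondary models, where the outcome's own baseline value is already a covariate if the same procedure is followed.

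The cost is a slightly longer model. Four single-coefficient covariates, each with two time-interaction terms, add 4 × (1 + 2) = 12 coefficients, which is small against 100 completers per group. No new data are needed. The sentence should be fixed before any outcome data are examined, since the same choice made later would look data-driven.
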